#### Cardiac Magnetic Resonance (CMR)

All subjects undergo CMR using a 3 Tesla-scanner (Magnetom Vida, Siemens, Healthcare, Erlangen Germany) after abstaining from caffeine and xanthine for 24 h. Figure 4 shows an overview of the imaging sequence protocol.

**Figure 4 F4:**
[figure not shown]
CMR protocol. The CMR-protocol consist of stress- and rest imaging, including long axis cine imaging to quantify left ventricular function, myocardial T1-mapping to quantify extracellular volume fraction, perfusion scans including adenosine stress and rest perfusion scan to quantify perfusion using myocardial perfusion reserve index (MPRi), and late gadolinium enhancement (LGE) imaging which is performed to characterize myocardial tissue together with native T1-mapping. Hyperenhancement with LGE is used to quantitatively assess myocardial infarct scar burden. CMR, cardiac magnetic resonance; LAX, long axis; SAX, Short axis; IV, intravenous; AIF, Arterial input function.

Myocardial perfusion imaging is performed during stress and rest, using a dual sequence technique optimized for quantification of absolute myocardial blood flow. For this purpose, three short axis images (base, mid-LV and apex) will be acquired during first-pass perfusion imaging, both during adenosine stress (adenosine infusion 140 μg/kg/min) and at rest, during administration of an intravenous bolus of contrast gadolinium (Dotarem 0.075 mmol/kg). Stress perfusion CMR-derived MPRI will be calculated (Figure 5).

**Figure 5 F5:**
[figure not shown]
Quantitative perfusion CMR. Quantitative perfusion CMR. **(A)** Rest MBF on SAX of the basal, mid-LV and apical slice, **(B)** Stress MBF on SAX of the basal, mid-LV and apical slice, **(C)** Polar maps demonstrating rest and stress MBF in each segment, **(D)** Polar maps of rMPR and MPRI in each segment. CMR, cardiac magnetic resonance; MBF, myocardial blood flow; SAX, short-axis images; LV, left ventricle; rMPR, relative myocardial perfusion reserve; MPRI, myocardial perfusion reserve index.

T1-mapping is applied to assess MBV and extracellular volume (ECV). For this purpose, short-axis images at mid-ventricular level and 4-chamber long axis images are acquired using the MOdified Look-Locker Inversion (MOLLI) sequence with a 5S(3s)3s sampling scheme, during rest and adenosine injection (adenosine infusion 140 μg/kg/min) and after administration of gadolinium (47, 48).

All CMR images are collected centrally and are analyzed using Circle (Circle Cardiovascular Imaging Inc., Calgary, Alberta, Canada).

#### Peripheral Microvascular Function

The EndoPAT (Peripheral Artery Tonometer, Itamar Medical, Israel) is a device used to non-invasively assess microvascular function. By using the EndoPAT insight is given in the functioning of the endothelial and smooth muscle cells of the patients as well as the healthy controls, since this latter group does not undergo CFT. The EndoPAT is non-operator-dependent, and records post-ischemic reactive hyperemia known as the PAT (Peripheral Arterial Tone) signal using plethysmographic probes. These probes are placed on the index finger of both hands. First a baseline flow-signal is obtained for 5 min. Subsequently, flow-mediated changes are evoked by occluding blood flow through the brachial artery using an inflatable blood-pressure cuff. After 5 min of inflation the cuff is deflated, which induces reactive hyperemia. During this hyperemic period, a second flow measurement is performed (49).

The EndoPAT displays the pulse amplitude response to hyperemia, and automatically calculates the Reactive Hyperemia Index (RHI) as the post-to pre-occlusion PAT-ratio on the index finger of the occluded arm, divided by the corresponding ratio from the contralateral, control arm (49, 50). The RHI is assumed to reflect systematic microvascular function, and a cut-off value of RHI <1,67 is used to diagnose peripheral microvascular dysfunction (51).

## Objectives

The primary objective of the MICORDIS study is a difference in MBV in INOCA patients compared to healthy controls, evaluated at baseline, during hyperinsulinemia and during increased myocardial contraction. Secondary objectives of the study are (1) sex differences in MBV, MBF, ΔMBV, baseline characteristics, cardiovascular risk factors, depression, stress level, blood parameters and physiological indexes in patient group, (2) differences in baseline characteristics, cardiovascular risk factors, depression, stress level and physiological indexes between patient and control group, (3) comparison of MBV, MBF and ΔMBV at baseline and after HE-clamp and dobutamine of the patient and control group, (4) MBV, MBF and ΔMBV compared between insulin resistant subjects and non-insulin resistant subjects, (5) correlation between MBV (+other related variables) measured with MCE and MBV measured with CMR, (6) difference in peripheral endothelial function between INOCA patients and healthy controls, and (7) differences in protein expression and phosphorylation of microvascular endothelial cells compared between patient and control group.

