## Statistical Analysis and Sample Size Calculation

The expected effect size was estimated based on a study of Rinkevich et al. (52). Rinkevich compared the MBV between healthy controls and patients with Syndrome X using dipyridamole as a stimulus of MBV. A reduced MBV in non-obstructive CAD patients compared to healthy controls is the primary endpoint of our study. We expect the difference in MBV to be greater during stimulation with insulin and dobutamine, compared to dipyridamole as stimulus on MBV, making the data of Rinkevich appropriate for the use of sample size calculations. To detect a mean difference in MBV of 25 (MBV determined with MCE is dimensionless), we calculated a sample size of 24 patients per group to achieve a power of 80%, assuming a standard deviation of 30 in both groups. This calculation assumed the 5% significance level, using a two-sided independent sample *t*-test. To account for a projected dropout of 15%, the study population consist of 28 INOCA patients (14 males and 14 females) and 28 healthy controls (14 males and 14 females). The primary analyses of the study consist of a comparison of MBV at baseline, during hyperinsulinemia and during increased MVO2, and will be corrected for multiple testing using the Bonferroni method. Based on the distribution of continuous outcomes, independent samples *t*-test or Mann–Whitney *U* test are used as appropriate.

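### The patient–control comparison of MBV is listed as both the primary objective and part of secondary objective 3, while the multiplicity correction is tied only to the primary listing; list it once, and use Holm in place of Bonferroni

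*Protocol article*

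**What the plan says.** All references are to the protocol article.

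- **Objectives, primary:** "a difference in MBV in INOCA patients compared to healthy controls, evaluated at baseline, during hyperinsulinemia and during increased myocardial contraction".
- **Objectives, secondary item 3:** "comparison of MBV, MBF and ΔMBV at baseline and after HE-clamp and dobutamine of the patient and control group".
- **Statistical Analysis and Sample Size Calculation, primary analyses:** they are defined by content as a "comparison of MBV at baseline, during hyperinsulinemia and during increased MVO2, and will be corrected for multiple testing using the Bonferroni method".
- **Same section, significance level:** the only level printed belongs to the sample size: "This calculation assumed the 5% significance level, using a two-sided independent sample" *t*-test. Its inputs are a mean MBV difference of 25, an SD of 30 in both groups, 80% power and 24 per group.

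The article gives no significance level for any secondary objective.

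**The concern.** The HE-clamp is how the study produces hyperinsulinemia, and dobutamine is how it increases contraction and MVO2. The MBV part of objective 3 therefore appears to be the primary comparison under another label: same outcome, same two groups, same three conditions. The correction is attached to one of the two listings.

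The question at stake is the study's main one, whether MBV is reduced in INOCA. If an MBV comparison gives a p-value between 0.0167 and 0.05, it fails the corrected primary test. An author could still report it under objective 3 without correction and call it significant. The objectives as worded do not rule that out.

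**Working it through.** **1. Set the two objectives side by side.**

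| | Primary objective | Secondary objective 3 |
|---|---|---|
| Outcome | MBV | MBV, MBF, ΔMBV |
| Groups | INOCA patients, healthy controls | patient group, control group |
| Conditions | baseline, hyperinsulinemia, increased contraction | baseline, after HE-clamp, after dobutamine |
| Multiplicity rule in the article | Bonferroni | none stated |

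MBV level overlaps fully. MBF and ΔMBV do not overlap. The wording of objective 3 is also loose on its own terms: the MCE section defines the insulin-induced ΔMBV as the difference between baseline and hyperinsulinemia, so it has no value at baseline.

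**2. Reproduce the planned sample size.** Inputs from the statistical section: difference 25, SD 30, two-sided alpha 0.05, power 80%. The standardised difference is 25/30 = 0.833. The exact two-sample t calculation gives n = 23.6, so 24 per group, with power 80.7% at n = 24. The stated figure reproduces.

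**3. Locate the zone where a corrected and an uncorrected reading differ.**

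- Bonferroni level over three tests: 0.05/3 = 0.0167.
- Standard error of the difference: 30 × √(2/24) = 8.66.
- Critical t on 46 degrees of freedom: 2.013 at 0.05 and 2.485 at 0.0167 (two-sided).
- Smallest significant observed difference: 2.013 × 8.66 = 17.4 at 0.05, and 2.485 × 8.66 = 21.5 at 0.0167.

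Observed differences from about 17.4 to 21.5 are the zone. If the true difference is the planned 25, power is 80.7% at 0.05 and 65.6% at 0.0167. A given comparison then lands in the zone 80.7 − 65.6 ≈ 15% of the time.

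**4. Compare Holm with Bonferroni for the three primary tests.** Holm orders the three p-values, compares the smallest with 0.05/3 = 0.0167, the next with 0.05/2 = 0.025 and the largest with 0.05, and stops at the first failure. Everything Bonferroni rejects, Holm rejects too.

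Simulation assumptions: normal data, 24 per group, 60,000 replicates per setting, correlation between conditions assumed at 0, 0.3, 0.5 and 0.8 because the article gives none.

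- *No true difference anywhere:* the chance of at least one rejection is 3.6–4.9%. It is identical for the two methods, because both make a first rejection only if the smallest p-value passes 0.0167.
- *Difference of 25 at all three conditions:* power per comparison is about 66% with Bonferroni. With Holm it is 75.5%, 74.5%, 74.2% and 72.4% at the four correlations.
- *Difference of 25 at the two stimulated conditions only:* power for each of those two is about 66% with Bonferroni and about 69% with Holm.

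**The case against.** The strongest reply is that the article never gives the test two thresholds. The 5% level is an input to the sample size and is not assigned to secondary objectives. The statistical section defines the corrected analyses by content, so Bonferroni can fairly be said to govern MBV at these conditions wherever it is listed. The labels primary and secondary already rank the two listings. This stands. A reader might infer that the same contrast is tested at 0.0167 and again at 0.05, and that the false-positive rate over the three tests rises to as much as 1 − 0.95³ = 14.3% (independent tests). The article does not support that, because the second level would have to be supplied by the reader.

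The absence of a secondary alpha or an exploratory label is no fault either. A condensed article may leave both to the full protocol or analysis plan.

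Objective 3 can also be read as change across conditions within each group, since it lacks the explicit between-group wording of objectives 2, 6 and 7. That reading is possible, although the only tests named for continuous outcomes are independent-samples tests, which do not fit paired change. If it is what is meant, the sentence needs rewording to say so.

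Finally, Bonferroni is valid and Holm corrects no error. This is also true: Holm is offered as a gain in power at no cost in error control.

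**Conclusion.** The point holds in a limited form. MBV level is listed in two tiers, the correction is tied to one of them, and the text leaves an opening for an uncorrected reading. Taken alone, the double listing is close to editorial. It is worth closing because it concerns the primary question and because the zone it opens, observed differences of about 17.4 to 21.5, lies just below the planned difference of 25.

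Those cut-offs assume 24 evaluable participants per group, an observed SD of 30 and the t-test. They would differ for the Mann–Whitney test or if more than 24 per group complete. The 15% chance of landing in the zone assumes a true difference of 25 at the condition concerned.

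The more useful change is Holm. Power per comparison rises from about 66% to about 74% (72–76% over the assumed correlations) if the planned difference holds at all three conditions, and to about 69% if it holds at two. Error control does not depend on these assumptions; the size of the gain does. That the starting power is 66% and not 80%, because the sample size used an uncorrected 5%, is a separate matter that this point does not rely on.

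**What to change.** 1. **Objectives, secondary item 3.** Remove MBV level, so that the item covers the between-group comparison of MBF and ΔMBV. If change across conditions within each group is intended, say so explicitly. Either way, the patient–control comparison of MBV level is then tested once, under the corrected primary rule.
2. **Statistical Analysis and Sample Size Calculation.** Where the primary analyses "will be corrected for multiple testing using the Bonferroni method", specify Holm's step-down procedure for the three MBV tests instead.

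**Cost.** The change is one clause in the objectives and one in the statistical section, with no new data or participants. The Trial Status section reports eight patients and three controls enrolled, so both edits can be made well before analysis. There are two small downsides. An MBV result that fails the corrected rule can no longer be presented as a secondary finding. Simultaneous confidence intervals that match Holm are less simple to construct than Bonferroni intervals.

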## Statistical Analysis and Sample Size Calculation

The expected effect size was estimated based on a study of Rinkevich et al. (52). Rinkevich compared the MBV between healthy controls and patients with Syndrome X using dipyridamole as a stimulus of MBV. A reduced MBV in non-obstructive CAD patients compared to healthy controls is the primary endpoint of our study. We expect the difference in MBV to be greater during stimulation with insulin and dobutamine, compared to dipyridamole as stimulus on MBV, making the data of Rinkevich appropriate for the use of sample size calculations. To detect a mean difference in MBV of 25 (MBV determined with MCE is dimensionless), we calculated a sample size of 24 patients per group to achieve a power of 80%, assuming a standard deviation of 30 in both groups. This calculation assumed the 5% significance level, using a two-sided independent sample *t*-test. To account for a projected dropout of 15%, the study population consist of 28 INOCA patients (14 males and 14 females) and 28 healthy controls (14 males and 14 females). The primary analyses of the study consist of a comparison of MBV at baseline, during hyperinsulinemia and during increased MVO2, and will be corrected for multiple testing using the Bonferroni method. Based on the distribution of continuous outcomes, independent samples *t*-test or Mann–Whitney *U* test are used as appropriate.

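### The sample size assumes one test at 5%, but the primary analysis is three Bonferroni-corrected tests, so power per comparison is about 66%, not 80%

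*Protocol article*

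**What the plan says.** All of the relevant text is in one paragraph of the Protocol article, under Statistical Analysis and Sample Size Calculation.

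- Target effect: "To detect a mean difference in MBV of 25", "assuming a standard deviation of 30 in both groups".
- Test and level: "This calculation assumed the 5% significance level", "using a two-sided independent sample *t*-test".
- Result: "we calculated a sample size of 24 patients per group to achieve a power of 80" (percent). This is raised to 28 per group for 15% dropout.
- Primary analysis: MBV is compared between patients and controls in three conditions (baseline, hyperinsulinemia, increased MVO2), and these comparisons "will be corrected for multiple testing using the Bonferroni method".

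The Objectives section names the same three conditions under the primary objective. The effect size is taken from an earlier study that used dipyridamole as the stimulus. The article expects a larger difference under insulin and dobutamine but gives no figure for it. It does not say which comparison the 80% refers to, or whether one significant result out of three would be enough.

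**The concern.** The sample size is worked out for a test that will not be run. Three primary tests under Bonferroni each use 0.0167, while the calculation uses 0.05. A stricter level with the same number of participants means lower power, so the 80% cannot hold for an individual comparison at the planned difference.

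This matters because the study asks about rest, insulin and stress separately. If the true difference is 25, each comparison would miss it about 34% of the time (100 − 65.6), not the 20% that readers would infer. A non-significant result in one condition would then look like stronger evidence of no difference than it is.

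The baseline comparison has a further weakness. The assumed difference of 25 was observed under a stimulus, and no effect size is given for the unstimulated state, yet that comparison takes a third of the alpha.

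**Working it through.** **Inputs** (all from Statistical Analysis and Sample Size Calculation): difference 25; SD 30 in each group; two-sided independent-samples t-test; alpha 0.05 in the calculation; 24 completers and 28 enrolled per group; dropout 15%; three primary comparisons; Bonferroni.

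**Formula.** Standardised effect d = 25/30 = 0.833. With n per group, the t statistic has 2n − 2 degrees of freedom and noncentrality d × √(n/2). Power is the probability that the noncentral t exceeds the two-sided critical value in absolute size.

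**Step 1: reproduce the plan's figure.** At n = 24, noncentrality = 0.833 × √12 = 2.887, and the critical value at 0.05 with 46 df is 2.013. Power is 80.7%. Solving for 80% gives n = 23.6, rounded up to 24. The plan's figure is right for a single test at 5% and contains no hidden allowance for multiplicity.

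**Step 2: use the planned level.** 0.05/3 = 0.0167. The critical value with 46 df rises to 2.485; the noncentrality is unchanged.

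| Evaluable per group | Power at 0.05 | Power at 0.0167 |
|---|---|---|
| 23 | 78.9% | 63.3% |
| 24 (plan's target) | 80.7% | 65.6% |
| 28 (no dropout) | 86.5% | 73.9% |

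The row for 23 is the cautious rounding of 28 × 0.85 = 23.8.

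**Step 3: what 80% would need at 0.0167.** Either n = 31.6, so 32 completers per group, or, with 24 per group, a true difference of 28.9 (d = 0.964). If 32 completers were wanted, enrolment would be 32/0.85 = 37.6, so 38 per group (76 in total against 56 planned).

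**Step 4: other readings of power.** These need the correlation between a participant's three MBV measurements, which the document does not give. The ranges below are assumptions, from simulated trials (at least 20,000 per setting) with 24 per group and Bonferroni.

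| True differences | Correlation | At least one significant | All three significant |
|---|---|---|---|
| 25 in all three | 0.3 | 91% | 36% |
| 25 in all three | 0.7 | 83% | 47% |
| 25 in all three | 0.9 | about 76% | about 55% |
| 25 in the two stimulated conditions, 0 at baseline | 0.3 to 0.7 | 85% to 78% | – |
| 25 in one condition only | 0.3 to 0.7 | about 67% | – |

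**Step 5: Holm instead of Bonferroni.** Same simulation, correlation 0.3 to 0.7. Power per test is about 73–74% if all three differences are 25, and about 68–69% for each stimulated test if baseline does not differ. If only one condition differs, Holm gives practically no gain (about 66%).

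**The case against.** Three arguments on the other side carry weight.

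*Larger effects under insulin and dobutamine.* The article expects the stimulated differences to exceed the dipyridamole value. At 0.0167 with 24 per group, a difference of 28.9 gives 80% and 30 gives 83%, so an effect about 16% larger (28.9/25 = 1.16) would restore the claim for two of the three tests. This is plausible. But the expectation is not quantified, the calculation itself uses 25, and baseline is not covered.

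*The 80% was never said to apply to each comparison.* If one significant result out of three suffices, power is above 80% for moderate correlations when all three differences are 25. That is true, but no such criterion is stated, and it is not how the 80% was derived. It falls to about 76% at a correlation of 0.9 and to about 67% if only one condition differs.

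*Bonferroni is valid.* It is. The familywise error is controlled as planned and no estimate is biased. The fault is confined to the power statement and its disagreement with the analysis, and 24 is correctly computed for the inputs used. It also stands that Holm recovers only part of the loss, and that a fixed order protects only the first test.

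None of this reconciles the level used for sizing with the level used for testing.

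**Conclusion.** The concern holds. The paragraph sizes the study at one significance level and analyses it at another. At the planned difference of 25 and SD of 30, power per primary comparison is 65.6% with the 24 completers aimed for, about 15 percentage points below the claim (80.7 − 65.6 = 15.1), and 73.9% at best if nobody drops out. These figures rest only on the article's own inputs and an equal split of alpha over three tests. Statements about at least one or all three comparisons also depend on an assumed correlation and on the true baseline difference, neither of which is given. The error should be corrected because it concerns the stated power of the primary analysis.

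**What to change.** 1. **Correct the power statement; keep 28 per group.** For example: at the Bonferroni level of 0.0167, 24 completers per group give about 66% power per comparison for a difference of 25 (SD 30), and 80% power for a difference of 28.9. Add what counts as a positive primary result, and say that the assumed difference comes from a stimulated setting and is not specific to baseline.
2. **Replace Bonferroni by Holm.** It controls the same familywise error and can never reject less. The gain depends on how many conditions truly differ (about 73–74% per test if all three do), so the corrected statement in item 1 is still needed.
3. **Optional alternative to item 2:** test in a prespecified order at 5% each, stimulated conditions first. The first test keeps about 80%; later tests count only if every earlier one succeeds. The investigators would have to choose and justify the order.

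Cost: revised sample size and multiplicity text, and a less favourable power figure. No extra participants are needed. Items 2 and 3 change the prespecified primary testing procedure, so they should be documented and dated before any MBV comparison is made. Trial Status reports eight patients and three controls enrolled, so this was feasible when the article was written.

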**Figure 3 F3:**
[figure not shown]
Myocardial contrast echocardiography. Contrast-enhanced transthoracic apical 4-chamber view end-systolic. After microbubble destruction with a high MI-pulse, replenishment of contrast is visible in the myocardium. **(A–C)** Subsequent replenishment of myocardial contrast, **(D)** ROI in the myocardial septum, **(E)** Example of myocardial replenishment in a time-video intensity curve. Fluctuations in the myocardial blood volume during replenishment, as demonstrated in this figure, is caused by the cardiac cycle of systole and diastole. MI, mechanical index; ROI, region of interest; M, myocardial; LV, left ventricle.

MCE is performed using the Philips iE33 (Philips Healthcare, Eindhoven, The Netherlands) ultrasound machine and is performed at baseline, after 2 h of hyperinsulinemia and during intravenous infusion of dobutamine. Following the first MCE-measurement at baseline, hyperinsulinemia is induced using the hyperinsulinemic-euglycemic (HE) clamp technique, developed by DeFronzo et al. (44). The goal of HE-clamping is to raise insulin plasma concentrations to postprandial levels while maintaining normoglycemia. During HE-clamp insulin and glucose are simultaneously infused to minimize the effect of hyper- and hypoglycemia.

At the start of the HE-clamp, the blood glucose level is measured. The clamp starts with two boluses of insulin, to lower stress-induced hyperglycemia. The first dose is 5 min of 4 times the normal insulin dose and the second bolus is 5 min of 2 times the normal insulin dose. The normal insulin dose is calculated with the formula: body surface area ^*^ 0,04 ^*^ 60 (45). After 10 min insulin is infused in a continuous rate of 40 mU/m (2) for 110 min. Infusion of 20% glucose solution is initiated simultaneously to maintain normoglycemia. During the administration of insulin, the blood glucose level is measured in 5 min intervals, and the glucose infusion rate is adjusted to maintain normoglycemia (i.e., blood glucose between 5 and 5.5 mmol/l). After 120 min of HE-clamp, steady-state glucose uptake has been reached and MCE is repeated.

The insulin-induced ΔMBV is the difference between MBV at baseline and during hyperinsulinemia. The amount of glucose infused between the 90 and 120 min steady-state insulin concentration during the HE-clamp, divided by body weight and time can be used to quantify the M-value (μmol/kg/min). The M-value represents the metabolic insulin-resistance (44, 46).

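### Single-step Bonferroni for the three primary MBV comparisons is valid but needlessly conservative; Holm's step-down rule holds the same 5% family-wise error and never rejects less

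*Protocol article*

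**What the plan says.** Under Myocardial Contrast Echocardiography (MCE) in the Methods, the protocol article states that the measurement "is performed at baseline, after 2 h of hyperinsulinemia and during intravenous infusion of dobutamine". Each participant therefore contributes three MBV values. The Objectives section sets the primary objective as a patient-control difference in MBV evaluated at these three conditions.

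Statistical Analysis and Sample Size Calculation describes the primary analyses as a "comparison of MBV at baseline, during hyperinsulinemia and during increased MVO2, and will be corrected for multiple testing using the Bonferroni method". Each comparison is an independent-samples t-test or a Mann–Whitney U test, depending on the distribution.

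The same section gives the design values: "To detect a mean difference in MBV of 25", "to achieve a power of 80%, assuming a standard deviation of 30 in both groups", and "we calculated a sample size of 24 patients per group". The calculation is for one test: "This calculation assumed the 5% significance level, using a two-sided independent sample" t-test. Enrolment is 28 per group to allow for dropout.

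The article states no correlation between conditions and no separate difference for baseline. For the stimulated conditions it says: "We expect the difference in MBV to be greater during stimulation with insulin and dobutamine, compared to dipyridamole as stimulus on MBV".

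**The concern.** The plan names a particular multiplicity rule, so this is a question about a stated choice and not about missing detail. Single-step Bonferroni compares every p-value with 0.0167, whatever the other two results are. Holm starts at the same threshold for the smallest p-value. Once that test is rejected, it relaxes to 0.05/2 = 0.025 for the next and 0.05 for the last. For the hypothesis tests, the stricter single-step rule buys no extra error control.

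The stake is how a mixed set of results is read. The study applies different stimuli to learn how MBV is regulated. If MBV is in fact reduced at every condition, a result that is significant at one or two of the three invites the reading that the deficit is specific to rest, insulin or dobutamine. A rule with more power at the same error rate makes that pattern less frequent.

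**Working it through.** **Inputs from the protocol article (Statistical Analysis and Sample Size Calculation):** difference 25, SD 30, two-sided alpha 0.05, 80% power, 24 per group (28 enrolled), three primary comparisons.

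**Assumptions, because the article gives no value:** within-person correlation ρ between conditions of 0.5, range 0 to 0.9; normally distributed MBV; the pattern of true differences, varied below.

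**Step 1. The plan's own figure.** The standardised difference is 25/30 = 0.833. A two-sided two-sample t-test (noncentral t) at alpha 0.05 and 80% power needs 23.6, so 24 per group. Power at 24 is 80.7%. The stated figure reproduces.

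**Step 2. Power under the stated rule.** The Bonferroni level is 0.05/3 = 0.0167. The same t-test at this level has 65.6% power per comparison with 24 per group and 73.9% with 28. These values do not depend on ρ.

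**Step 3. Holm.** Order the p-values p(1) ≤ p(2) ≤ p(3). Reject the first if p(1) ≤ 0.05/3, then the second if p(2) ≤ 0.05/2, then the third if p(3) ≤ 0.05, and stop at the first failure. Power depends on the joint distribution, so it was simulated with three correlated t-tests and 100,000 trials per setting. The gains come from the paired simulation and can differ by a few tenths of a point from subtraction of the rounded powers.

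True difference 25 at all three conditions, 24 per group:

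| ρ | Bonferroni, per comparison | Holm, per comparison | Gain (points) |
|---|---|---|---|
| 0 | 65.6% | 75.6% | 9.9 |
| 0.3 | 65.6% | 74.7% | 8.9 |
| 0.5 | 65.6% | 73.9% | 8.3 |
| 0.7 | 65.6% | 72.9% | 7.5 |
| 0.9 | 65.6% | 71.9% | 6.1 |

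At ρ = 0.5 the chance of showing all three differences is about 41% with Bonferroni and 60% with Holm. With 28 per group and ρ = 0.5, power per comparison is 74% versus 82%, and all three are shown in 52% versus 70% of trials.

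**Step 4. Other patterns of true differences** (24 per group, ρ = 0.5):

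| Baseline / insulin / dobutamine | Gain at baseline | Gain for each stimulated comparison |
|---|---|---|
| 25 / 30 / 30 | 12 points (65.5% to 77.3%) | 5 points |
| 12.5 / 25 / 25 | 11 points (16% to 27%) | 4 points |
| 0 / 25 / 25 | no true difference | 3.5 points |
| 0 / 0 / 25 | no true difference | about 0 for the one real difference |

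For 0 / 25 / 25 the gain runs from about 4 points at ρ = 0 to about 3 at ρ = 0.8.

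**Step 5. What does not change.** The first Holm threshold equals the Bonferroni threshold, so the chance of at least one significant result is identical under both rules (about 88% for 25 / 25 / 25 at ρ = 0.5). For the same reason the family-wise error when no difference is real is identical: 4.9%, 4.4% and 3.6% at ρ = 0, 0.5 and 0.8.

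**Step 6. Mixed results.** With 25 / 25 / 25, ρ = 0.5 and 24 per group, one or two of the three are significant in about 46% of trials with Bonferroni and 28% with Holm.

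**The case against.** The strongest reply is that the plan contains no error. Bonferroni controls the family-wise error under any dependence, it is simple and familiar, and it gives matching simultaneous confidence intervals. In a mechanistic study of 28 per group, that last property is a fair reason to keep it. This stands: the point concerns efficiency, not validity.

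Three stronger readings are tempting, and the article does not support them.

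- A reader might infer that testing repeated measurements separately is itself a mistake. It is not. Each test compares patients with controls at one condition. Holm also runs three separate tests and makes no use of the correlation; its gain shrinks as the correlation rises.
- A reader might infer a fixed loss of about 8 points per comparison. That figure needs a difference of 25 at all three conditions and a correlation near 0.5. The article gives no correlation and no baseline difference, and it expects larger differences under insulin and dobutamine than in the dipyridamole comparison it used.
- A reader might infer that Bonferroni will probably produce a misleading mixed result. At a correlation of 0.5 this occurs in about 46% of trials, and Holm still leaves 28%. Neither rule prevents someone from treating a non-significant result as evidence of no difference.

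The all-three figure also uses a success criterion that the article does not set, so it describes the design and is not a failed target.

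Finally, the sample size uses alpha 0.05 for a single test while the primary tests are corrected. That is a separate matter. Holm does not resolve it: with differences of 25 and 24 per group, it reaches about 72% to 76% per comparison, not 80%.

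**Conclusion.** The point holds as a cheap improvement. The stated rule is valid but gives up power, since Holm offers the same 5% family-wise control under any dependence and never rejects less. If all three differences are 25 with SD 30, 24 per group are evaluable and the correlation is 0.5, power per comparison rises from about 66% to 74%. In the less favourable patterns tried, the benefit to the stimulated comparisons is a few points or nothing. The size therefore rests on assumed correlations and effect patterns. The direction does not: in no pattern does Holm do worse on the tests.

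**What to change.** In Statistical Analysis and Sample Size Calculation, replace the reference to Bonferroni with wording such as: *using the Holm step-down procedure across the three conditions (ordered p-values against 0.05/3, 0.05/2 and 0.05)*. The rule works on p-values, so it applies whether the t-test or the Mann–Whitney U test is used. It should be fixed before the data are analysed, because a switch made after seeing p-values would not be credible. The Trial Status section reports eight patients and three controls enrolled, so at that stage there was still time.

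The cost is one sentence, with no added patients or measurements. The downside is that Holm has no simple simultaneous confidence intervals. Report Bonferroni-level or unadjusted 95% intervals alongside the tests, and state which is used. Bonferroni-level intervals may include zero for a comparison that Holm rejects, and the text should say so.
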